## **8.6 Packaging, Labelling and Supply**

The packaging, blinding, labelling and storage of the medicine at all pharmacy sites conforms to the HMG, according to a randomisation list that is only known to the CTC Zürich as a whole and to the local pharmacy sites in part.

The individual pre-filled syringes will be allocated unequivocally by their labelling (centre, patient number). One vial will contain 2000 IU of EPO per ml and in total 3000 IU = 1.5 ml, this is the maximal amount per medication.

Each study site will order the medicine only patient-related and when a medication is scheduled. There will be no long-term storage, the medicine has to be administered within 7 days (shelf life). Adequate refrigeration (+2 to + 8°C) must be provided during short-term storage at the individual centres. Unused samples must be stored by the individual centres until the study monitor will have controlled and released the unused samples. Afterwards they can be disposed. Disposal of samples must be documented in a disposal protocol (included in the investigator's file).

Drug supply will be done as follows: The Kantonsapotheke Zürich (KAZ) will supply the study sites in Zurich, Aarau, Basel, Chur, Lausanne, and St. Gallen; the Spitalpharmazie of the Inselspital Bern the study site in Bern. In Germany, the Clinical Research Organization (CRO) of the University hospital in Berlin (Charité) will supply the respective study site. In Austria, the pharmacy of the University hospital in Wien will supply the study site in Wien.

The supply from Zurich to Aarau, Basel, Chur, Lausanne, and St. Gallen is organized as follows: After preparation of the study drug by the Kantonsapotheke Zurich, the study drug will be put in a transport cooling box, with guaranteed stability of temperature between 2 and 8°C for 24 hours (Neopor, STOROPack). Each box contains a temperature logger (Q-tag, Berlinger), which is used to monitor temperature during transport. After delivery the recipient at the local study site will charge the logger data electronically and will save the file for study monitoring. The study drug transport will be done by Swiss-Express Mond (Die Post) with personal pickup in the afternoon and delivery next morning.

Upon receipt of the study treatment supplies, an inventory must be performed and a drug receipt log filled out and signed by the person accepting the shipment. It is important that the designated study staff counts and verifies that the shipment contains all the items noted in the shipment inventory. Any damaged or unusable study drug in a given shipment (active drug or comparator) will be documented in the study files.

Regular study drug reconciliation will be performed to document drug assigned, drug consumed, and drug remaining. This reconciliation will be logged on the drug accountability form, and signed and dated by the study team.

## **8.7 Blinding**

The study is randomised on a double-blind basis. This means that the attending investigators do not know whether they are using the placebo or the verum. Randomisation is performed by the CTC Zürich on the basis of randomisation lists. Randomization lists for block randomization will be performed for each participating study site separately by the CTC Zürich.

In the event that debinding should be required subsequent to an individual patient's withdrawal from the study, this will be possible by immediate notification of the responsible pharmacy or the CTC Zürich, with specification of the centre and randomisation number, within 24 hours.

In the event of deblinding, the PI has to be notified within a period of 24 hours. The PI will then take charge of further reporting as required by the GCP guidelines.

An Emergency Code Break will be available to each investigator. This Code Break should be opened only in emergency situations when the identity of the investigational product must be known by the investigator in order to provide appropriate medical treatment.

### **8.8 Storage Conditions**

On each neonatology ward only short term storage is necessary, maximum 7 days. For this purpose adequate refrigeration (+2 to + 8°C) and protection from light will be performed in the refrigerator for medications for which limited access is given.

### **8.9 Study Drug Accountability**

The study drug supplied on request to the local PIs will be kept in a secure, limited access storage area under the recommended storage conditions.

The local PIs will maintain accurate and adequate records including dates, lot number, quantities received, individual usage.

### **8.10 Return or Destruction of Study Drug**

At the completion of the study, there will be a final reconciliation of drug shipped, drug consumed, and drug remaining. This reconciliation will be logged on the drug accountability form, signed and dated. Any discrepancies noted will be investigated, resolved, and documented prior to return or destruction of unused study drug.

## 9 STUDY PROCEDURES

All patients will be assessed with regard to inclusion/exclusion criteria (sections 7.1 and 7.2). If the criteria are met, the patient shall be included in the study after written informed parental consent has been obtained. The study medication will be obtained from the responsible pharmacy. It will be supplied on request.

### 9.1 Study-related Procedures

#### Procedures during NICU hospitalization

The following tests are standard procedures performed routinely in all VLBW infants and especially in those with IVH > grade 1 independent of enrolment in the study (medically indicated tests and examinations). The local PIs will take care that the following tests will be done completely:

- Minimal electronic monitoring includes heart rate (or pulse rate) with recommended alarm limits at 90 and 180 beats per minute, arterial saturation (pulse oximetry) with recommended alarm limits at 85% and 95%.
- Arterial blood pressure will be monitored continuously if there is an indwelling arterial line and intermittently by oscillometric measurement at least daily during the first weeks.
- Serial determination of Hb and Hct is part of standard care, in the first days of life daily, when infants are stable then at least weekly until discharge.
- Serial cUS assessment will be carried out on day 1, 3, and at day 7 and then every 14 days until 36 /7 weeks postmenstrual age (or at discharge if discharged before) to detect intracranial haemorrhage, ventricular dilatation and white matter disease .
- MRI: There is clinical need to perform MRI in VLBW infants with severe IVH to determine precisely the extend of IVH especially if posthaemorrhagic hydrocephalus occurred and to predict outcome, which is important in counselling parents and managing follow-up. The access of each neonatology level III centre to MRI and the routine practice vary largely between centres. Also the timing of MRI is not standardized.
- Both eyes are examined by an ophthalmologist to detect retinopathy of prematurity (ROP). The severity of ROP will be graded according to the international classification of ROP.
- Necrotising enterocolitis (NEC) is diagnosed by clinical signs (abdominal distension, bilious aspirates, and/or bloody stools) and either pneumatosis intestinalis, hepatobiliary gas, or free intraperitoneal air on abdominal x-ray or at laparotomy. Severity of enterocolitis will be graded according to presence and severity of complications.
- Septicaemia is diagnosed by clear clinical, radiological, or biochemical evidence of infection and at least one microbiologically relevant positive blood culture.
- Persistent ductus arteriosus (PDA) is diagnosed clinically or with echocardiography and documented only if drug treatment (indomethacin or ibuprofen) or surgical ligation is required.
- Weight and head circumference are recorded at birth, at 7 to 10 days, at 36 /7 postmenstrual weeks, at 24 months and 5 years corrected age.
- Placental histology is regularly done in infants born very preterm. It identifies prenatal risks such as amnion infection and placental malfunction.
- Adaptation after birth will be documented with the Apgar score at 1, 5 and 10 minutes.
- The Clinical Risk Index for Babies (CRIB). The CRIB is a simple tool for assessing neonatal risk based on the variables gestational age, birth weight, congenital malformations, lowest and highest appropriate FiO2 and worst base deficit within the first 12 hours of life.

## **9.2 Study-specific Procedures**

Apart from the administration of study medication there is no procedure within this study which is not part of routine management of VLBW infants, including MRI in infants suffering from severe IVH. As the timing of MRI is not standardized the study-specific requirement is to perform MRI at term equivalent age, visit 4.

All items recorded by MRI are given in visit 4, section 6.7. In principal, the MRI for all VLBW infants will be performed at the site of hospitalisation. If discharge home occurred before time point of visit 4, VLBW infants will be invited to come together with their mother to the MRI, which will be performed in natural sleep. This occurs usually after feeding and is sufficient to keep the infant quiet enough for MRI. In general, no medications will be given and no line will be installed. This procedure has been established during the first EPO trial at the study centre in Zurich (USZ). However, as the MRIs will be performed not only at the USZ, other study sites may have different approach for keeping the infant quiet during MRI. These specific in-house approaches are acceptable within this study and are in the responsibility of the local doctors.

## **9.3 Sample preparation, storage, and shipment**

There is no collection of study samples planned, e.g. blood or tissue. However, the cUS and MRI files will be saved together with patient records.

Please see also chapter 6.10 for an addendum

## 10 SAFETY

The Sponsor's SOPs provide more detail on safety reporting.

### 10.1 Definition of (Serious) Adverse Events

#### Adverse events

Adverse events (AEs) are defined as any untoward medical occurrence in a patient or clinical investigation subject administered a pharmaceutical product and which does not necessarily have a causal relationship with this treatment. An AE can therefore be any unfavourable and unintended sign (including an abnormal laboratory finding), symptom, or disease temporally associated with the use of a medicinal study product, whether or not related to the medicinal study product. An AE may also consist of a new disease, an exacerbation of a pre-existing illness or condition, a recurrence of an intermittent illness or condition, a set of related signs or symptoms, or a single sign or symptom.

AEs observed by the investigator and/or reported by the caregivers or parents must be reported in the eCRF during the entire study period, the period of time from the first drug administration until discharge home.

For all AEs, sufficient information will be pursued and/or obtained so as to permit an adequate determination of the outcome of the event (i.e., whether the event should be classified as an SAE) and an assessment of the causal relationship between the AE and the investigational drug or study treatment(s).

Whenever available, the underlying disease or condition for which a therapeutic or diagnostic procedure is required should be reported as the AE term. Surgeries or other invasive procedures that had already been planned prior to the start of the study do not have to be documented as AEs. These planned procedures will be recorded in the eCRF by the investigator at the baseline visit. It is not important if the condition was known before enrolment, only if the procedure was planned before.

This trial enrolls highly vulnerable and largely immature neonates who are born very preterm and thus are unable to survive without intensive care support. Most organ functions are physiologically immature in the neonatal period. The degree of immaturity is aggravated due to prematurity. Prematurity is characterized by the absence of abilities a healthy born infant has a priori when born at term. These abilities include but are not limited to body water homeostasis, body temperature maintenance, skin vulnerability, stable breathing and heart rate, drinking, digestion, liver function, and host defense (Guideline on the investigation of medicinal products in the term and preterm neonate, EMA, June 2009, Doc. Ref. EMEA/536810/2008). Therefore, the preterm body shows a large number of different symptoms which are characteristic hallmarks of immaturity and which disappear gradually alongside maturation over a timespan of many weeks, see also the below given short list of symptoms typically present in all very preterm infants (further information is given e.g. in the textbook edited by Maier RF and Obladen M, Neugeborenenintensivmedizin – Evidenz und Erfahrung, Springer 2011).

In addition to this immaturity there are various signs, particularly affecting the skin, owing to intensive care and fixation of life saving devices mainly on the skin by plasters, stripes and patches. These devices include but are not limited to breathing tubes, feeding tubes, intravenous lines, electrodes and sensors. As a result, mainly the immature skin shows transient signs of fixation and positioning as listed below.

In conclusion of both, large immaturity and intensive care, all very preterm infants are characterized by a variety of signs which are typical and expected in this population and must not be considered as an AE. To clarify this, there is in addition to the list of immaturity signs and intensive care signs a third list providing samples of AEs, which comprise common deteriorations of very preterm infants but which are not regularly expected and may indicate

therefore any unfavourable and unintended sign, symptom, or disease temporally associated with the use of a medicinal study product, whether or not related to the medicinal study product.

1) Examples of immaturity signs not qualifying as AE:

- **Apnea and oxygen desaturations** occurring in all very preterm infants due to immaturity of brain and lung and are treated with caffeine, oxygen and if severe with respiratory support.
- **Episodes of bradycardia** occur in almost all very preterm infants often in combination with apnea and oxygen desaturation.
- **Edema** occurs in almost all very preterm infants after birth due to kidney immaturity and usually disappears within few weeks. Edema may affect the whole body if severe or only typical regions, such as eyes, hands and feet.
- **Jaundice** is usually present in the first and second week of very preterm infants due to liver immaturity.
- **Skin barrier damage** is the consequence of immature skin and may occur by simply lying on the skin or touching it. Skin of very preterm infants is highly vulnerable and in regard to treatment similar to that of burn victims.
- **Gastric residuals** are often present and mainly transient in the first weeks of life.
- **Hypothermia or hyperthermia** following inappropriate incubator temperature.

2) Examples of intensive care signs not qualifying as AE:

- **Local redness of the skin** occurs always after removal of e.g. plasters, sensors, strips and is visible for few hours but sometimes for days.
- **Local trauma of the skin including local haematoma** is unavoidable when performing a heel prick, vein puncture or other medically needed invasive procedures braking skin integrity. Afterwards the damage is visible for few hours but sometimes for days.

3) Examples of AEs:

- **Anaemia** needing blood transfusion (RBC-transfusion)
- **ROP** Grade: Mild: Grade 1 → **AE**  
Moderate: > Grad 1 or plus disease → **AESI**, see below  
Severe: needing intervention → **SAE**, see below
- **BPD** Grade: Mild: no AE  
Moderate: O2 < 30% mit 36. PMA → **AE**  
Severe: O2 ≥ 30% mit 36. PMA → **AE**  
Prolongation of hospitalization due to BPD beyond EDD (requiring any respiratory support because of BPD) → **SAE**
- **Posthaemorrhagic ventricular dilatation:**  
Moderate if ventricular dilation is > 97 centile → **AE**  
Severe if ventricular dilation is > 4 mm above 97th centile. → **AE**
- **Patent ductus arteriosus:** if medical treatment is required (not preventive) and/or surgical ligation
- **Incorrect drug applications**

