| Visit 4: Brain MRI                                                                                        |                       |         |                   |        |                | ■                      |                 |                 |
| Visit 5: BSID-III                                                                                         |                       |         |                   |        |                |                        | ■               |                 |
| Visit 6: K-ABC                                                                                            |                       |         |                   |        |                |                        |                 | ■               |
| Study medication                                                                                          |                       |         | ■                 |        |                |                        |                 |                 |
| AEs and SAEs                                                                                              |                       |         | ■                 | ■      | ■  |                        |                 |                 |
| Blood sampling for biomarkers                                                                 |                       | ■       |                   | ■      | ■              |                        |                 |                 |

■ compulsory (for medication, adverse events etc.)

1. Cranial ultrasound is performed regularly after birth (DOL 1-7), after 4 weeks (DOL 28) and before discharge at PMA 36 weeks, part of regular controls.
2. IMP: Investigational Medicinal Product
3. Continuous monitoring: heart rate, pulse oximetry, part of regular monitoring
4. Blood counts: haematocrit and haemoglobin, part of regular controls.
5. All new AEs and SAEs that the investigators will be notified of until discharge home have to be reported.
6. Blood sampling is performed only in few study sites as indicated in chapter 6.10

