### **10.2 Recording of (Serious) Adverse Events**

The well-being of the subjects will be ascertained by medical caregiver when subjects are hospitalized and the parents when subjects are discharged. Clinical investigators and ultimately the protocol PI have the primary responsibility for AE identification, documentation, grading, and assignment of attribution to the investigational agent/intervention.

All observed or volunteered adverse drug events (serious or non-serious) and abnormal test findings, regardless of treatment group or suspected causal relationship to the investigational drug or study treatment(s) will be recorded in the patient file and subsequently in the eCRF.

Recording will be done from first study treatment DOL 5 (-2/+3 days) until discharge home. As an exception the defined AEs (ROP grade  $>1$  or Plus diseases, BPD if classified as severe at 36 PMA, and anaemia) will be recorded without time limit.

AEs or abnormal test findings felt to be associated with the study treatment(s) will be followed until the event (or its sequelae) or the abnormal test finding resolves or stabilizes at a level acceptable to the investigator.

An abnormal test finding will be classified as an AE if one or more of the following criteria are met:

- The test finding is accompanied by clinical symptoms.
- The test finding necessitates additional diagnostic evaluation(s) or medical/surgical intervention; including significant additional concomitant drug treatment or other therapy

**Note:** simply repeating a test finding, in the absence of any of the other listed criteria, does not constitute an AE.

- The test finding leads to a change in study dosing or discontinuation of subject participation in the clinical study.

All AEs, serious and non-serious, will be fully documented in the appropriate eCRF. For each AE, the investigator will provide the onset, duration, intensity, treatment required, outcome and action taken with the investigational product.

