### **10.5 Follow up of (Serious) Adverse Events**

Subjects terminating the study (either regularly or prematurely) with

- reported ongoing SAE, or
  - any ongoing AEs of laboratory values or of vital signs being beyond the alert limit
- will return for a follow-up investigation. This visit will take place up to 30 days after terminating the treatment period. Follow-up information on the outcome will be recorded on the respective AE page in the eCRF. All other information has to be documented in the source documents. Source data has to be available upon request.

In case of subjects lost to follow-up, efforts should be made and documented to contact the subject to encourage him/her to continue study participation as scheduled.

All new SAE that the investigators will be notified until discharge home have to be reported in appropriate report forms and in the eCRF.

Follow-up investigations may also be necessary according to the investigator's medical judgment even if the subject has no AE at the end of the study. However, information related to

these investigations does not have to be documented in the eCRF but must be noted in the source documents.

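### General AE/SAE collection stops at discharge home, so new events at a later study-timed MRI need not be reported, and the SAP's 40-week safety window does not match what the protocol collects

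*Combined protocol and SAP*

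**What the plan says.** **Collection window.** Protocol 10.1 states that AEs "must be reported in the eCRF during the entire study period, the period of time from the first drug administration until discharge home". Section 10.5 repeats this for serious events: "All new SAE that the investigators will be notified until discharge home have to be reported in appropriate report forms and in the eCRF". Footnote 5 of the study schedule says the same: "All new AEs and SAEs that the investigators will be notified of until discharge home have to be reported". The AE/SAE row of the schedule has its last mark at 36 weeks PMA and none at term equivalent age. The visit 4 items in 6.7 include no AE field.

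**Exceptions.** Section 10.2 lifts the limit for three conditions: ROP above grade 1 or Plus disease, and "BPD if classified as severe at 36 PMA, and anaemia) will be recorded without time limit". Section 6.5 agrees.

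**The MRI.** Visit 4 is scheduled at 40 0/7 ± 3 weeks PMA (6.1). Section 9.2 calls its timing the study-specific requirement and expects some infants to be home by then: "If discharge home occurred before time point of visit 4, VLBW infants will be invited to come together with their mother to the MRI". Natural sleep, in general without medication or a line, is the described method, but "other study sites may have different approach for keeping the infant quiet during MRI", and this is accepted.

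**Analysis.** SAP section 7 describes AEs and SAEs up to 40 weeks PMA as frequencies and percentages by arm. It makes no adjustment for time at risk. SAP 5.2.2 separately compares time to hospital discharge between arms.

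**The concern.** An infant who has gone home is called back at a time set by the trial, yet nothing obliges the site to record a new event at that visit. Hospitalisation is itself a seriousness criterion in 10.1. A readmission after the scan would therefore qualify by definition and still fall outside the window. It would then get no causality assessment (10.3), no 24-hour report or place in the sponsor's monthly SAE export (10.4), and no review by the monitoring committee (10.6).

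Two further problems concern the comparison of arms. First, the window closes at discharge, which is an outcome of the trial, while the SAP reports raw percentages. Second, the SAP's cut-off at 40 weeks PMA is not the point at which the protocol stops collecting.

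**Working it through.** The plan gives no figure on this point, so there is nothing to reproduce. The check sets the windows side by side and then asks how many infants could be affected.

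**1. Coverage of a new event**

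| Where the infant is | Collected under protocol section 10? | Inside the SAP section 7 window? |
|---|---|---|
| In hospital, up to 40 weeks PMA | Yes | Yes |
| In hospital, after 40 weeks | Yes | No |
| Home, up to 40 weeks | Only the three exceptions | Yes, but general AEs are not collected |
| Home, after 40 weeks (MRI possible to 43) | Only the three exceptions | No |

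The second row matters for a named SAE. Sections 10.1 and 1 together define BPD as serious when it prolongs hospitalisation beyond the estimated date of delivery, which is 40 weeks. That criterion can be met only after the SAP's cut-off. The SAP does not say whether such an event would be dated back to the 36-week diagnosis.

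**2. Other routes**

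- The 10.5 follow-up visit is for ongoing events. T1 falls on DOL 3–8, so the last dose (16 days later) falls on DOL 19–24. Thirty days after that is DOL 49–54. At 29.3 weeks' gestation this is about 29.3 + 49/7 = 36.3 to 29.3 + 54/7 = 37.0 weeks PMA, before or just at the opening of the MRI window.
- The two-year visit (6.8) records first-year rehospitalisation and its main reason, but as a follow-up item and not as an SAE.

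**3. How many might be home first**

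Inputs come from the earlier EPO trial, tabulated in protocol 4.6: gestational age 29.3 weeks (SD 1.6) in both arms; days in hospital 54.2 (25.1) on EPO, n = 206, and 55.3 (25.1) on placebo, n = 189.

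- Pooled stay: (206 × 54.2 + 189 × 55.3)/395 = 54.7 days.
- Mean PMA at discharge: 29.3 + 54.7/7 = 37.1 weeks.
- SD of PMA at discharge: √(1.6² + (25.1/7)² + 2ρ × 1.6 × 25.1/7). This is 3.93 weeks for ρ = 0 and 2.50 for ρ = −0.8.

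Assumptions: normal distribution; correlation ρ between gestational age and stay from 0 to −0.8; stay 0 to 4 weeks longer in infants with IVH grade II–IV.

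| Extra stay (assumed) | Home before 37 weeks | Before 40 weeks | Before 43 weeks |
|---|---|---|---|
| 0 weeks | 48–49% | 77–88% | 93–99% |
| 2 weeks | 20–29% | 59–64% | 84–94% |
| 4 weeks | 5–15% | 33–39% | 68–77% |

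The extremes at 40 weeks are z = (40 − 37.1)/2.50 = 1.15, giving 88%, and z = (40 − 41.1)/2.50 = −0.45, giving 33%.

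**4. Dependence on length of stay**

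With T1 on DOL 5, the mean window on the same data is 54.7 − 4 = 50.7 days. One SD either side gives about 26 and 76 days. The earlier trial's arm difference was 55.3 − 54.2 = 1.1 days, or 1.1/50.7 = 2% of the window. A hypothetical 5-day difference would be 5/50.7 = 10%.

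**The case against.** The best defence is that the cut-off is reasonable for drug safety. At a mean stay of 54.7 days, collection runs about 31–36 days past a last dose on DOL 19–24. Protocol 4.4 cites a half-life of 8 hours after 200 U/kg. Death, sepsis, NEC, BPD, white matter disease and ROP are analysed as secondary outcomes in their own right, and the AE tables are descriptive. Safety signals go to the sponsor with no discharge limit (10.4), 10.2 looks to parents for well-being after discharge, and section 15 asks that health problems be notified. Sponsor SOPs may add more. All this lowers the stakes. None of it requires a new event on the day of the MRI to be entered as an AE or SAE.

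Several stronger readings are tempting, but the documents do not support them:

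- *Most of the 100 planned scans fall outside the window.* That needs a fixed scan date of 40 0/7 weeks and a population not restricted to IVH. The window opens at 37 weeks, scans are in principle done at the site of hospitalisation, and sites may scan before discharge. Section 6.1 itself expects discharge at about term equivalent age.
- *The arms are observed for different times.* The only data show 54.2 against 55.3 days (p = 0.67).
- *Infants are sedated.* The text allows a different approach and says no more.
- *Apnoea at the scan would be missed.* Section 10.1 lists typical apnoea among signs of immaturity that are not AEs, so a longer window need not capture it.
- *Grade II infants are scanned without clinical need.* Section 9.1 says "There is clinical need to perform MRI in VLBW infants with severe IVH", but its list is introduced as routine care, especially for IVH above grade 1, so the text is ambiguous.

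**Conclusion.** The point holds as a reporting gap and a mismatch between protocol and SAP. For infants discharged before visit 4, a new event at the study-timed MRI need not be reported as an AE or SAE. Those still in hospital are covered, and the three open-ended conditions are recorded wherever the infant is. The SAP's window to 40 weeks PMA runs past general collection for infants already home and stops short of it for those still in hospital.

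The number affected is unknown. The range of about 33–88% home by 40 weeks rests on the earlier trial's figures and the assumptions stated, and it is not a forecast of scans outside the window. Expected harm from the MRI is low, given natural sleep as the described method. A bias between arms through length of stay is possible in principle, but no evidence in the documents shows one. No sample size or error rate is affected. The change is worth making because it is cheap.

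**What to change.** **Protocol 10.1, 10.2, 10.5 and schedule (and 6.5, for consistency).** Collect AEs and SAEs from first dose until the latest of discharge home, completion of visit 4 and 40 0/7 weeks PMA. Add an AE mark at term equivalent age, and add to the visit 4 form one AE question and one field for any medication given for the scan.

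**SAP section 7.** Compare arms over the common window from first dose to 40 0/7 weeks PMA, which no longer ends at discharge. List later events separately, including those at visit 4 and the BPD SAE beyond the estimated date of delivery. Amending the protocol alone would not be enough: its window would still vary by infant, and events after 40 weeks would stay out of the analysis.

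**Infants already past visit 4.** Retrieve events from records where possible; otherwise state the limitation and report AE rates per time at risk. The SAP's reference list runs to 2019, after the planned end of recruitment in 2018, so this may be the only route for most infants.

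**Cost.** A short amendment, two form items at a visit that already takes place, slightly more AE entries, and some record review if done retrospectively.
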